### Anthropometry

Trained staff will measure height, weight and waist circumference following standardised operating procedures (eg, wearing light clothing, removing shoes). Age-specific and sex-specific body fat percentage will be calculated from bio-electrical impedance (collected using Tanita TBF 300 scales), age-specific and sex-specific BMI z-score will be calculated from height and weight. Quality checking of researchers’ anthropometry measurements will be conducted prior to baseline measurements and before 10-month follow-up.

### Questionnaires

At each measurement session (ie, T1, T2, T3 and T4), participants will complete a questionnaire concerning secondary outcomes, potential mediators or moderators, and items to monitor any adverse intervention effects. Physical activity type will be assessed using the 30-item Youth Physical Activity Questionnaire, which has previously been validated in 12–17-year-old adolescents.^44^ Self-efficacy^45^ and social support for physical activity^46^ will be assessed using two scales (each with three items). Further items include friendship quality (8-item Cambridge Friendships Questionnaire),^47^ well-being (14-item Edinburgh-Warwick Wellbeing Scale),^48^ self-esteem (10-item Rosenberg Self Esteem Scale^49^ and an adapted social network modelling tool in which participants are provided with a list of tutor group members and asked to select names of their friends),^50^ and shyness and sociability (two 5-item measures from EAS temperament scale).^51^ Questionnaires will be checked for completion before the end of the measurement sessions, and participants will be asked to complete any missing items. At T1, participants will respond to additional items providing demographic data (ie, age, sex, ethnicity, language spoken at home, parent education and family socioeconomic status). School-level attendance and academic performance (from National Pupil Database) will be collected (publicly available data).

### Process evaluation

Process evaluation will examine the proposed action model for the GoActive intervention (see online supplementary file 1). These process evaluation questions emulate those depicted in Saunders, Evans and Joshi’s process-evaluation plan to assess the implementation of a targeted health promotion intervention.^52^ We focus on six components: fidelity, dose (delivered and received), reach, recruitment and context.^52–54^ See online supplementary file 1 for the applicability and operationalisation of these components.

10.1136/bmjopen-2016-014419.supp1Supplementary data 1

Intervention process data will include mixed-methods assessment of student, mentor, facilitator, teacher and GoActive staff experiences, and perspectives on intervention delivery, feasibility, acceptance and barriers/facilitators to participation. Reach (eg, the intended amount of students that participate within the intervention) and dose received (eg, the proportion of students who enter points on the GoActive website, how often students download QuickCards and view videos) will be established using the points entries on the study website, download statistics for intervention materials and mentor-reported participation. Process evaluation questionnaires will be administered at T2 and T3 for students (both intervention and control), as well as mentors, facilitators and form teachers in intervention schools. Control participants will be asked to complete process evaluation questionnaires to determine possible contamination. We will include a GoActive logbook for the intervention facilitator and mentors to assess frequency of intervention delivery and any other descriptive notes at T2. Given the flexible, spontaneous and informal nature of the intervention (mentors/leaders attend the same school and can therefore encourage/motivate year 9 students at any time during the week), observation of all intervention delivery is not feasible; but classroom observation will be undertaken to complement other qualitative methods. Existing and emerging school practices which may affect students’ physical activity behaviour will be documented and monitored in a structured manner using an adapted school environment questionnaire.^53^

A qualitative researcher will conduct semistructured focus groups, using open-ended questions, after the facilitated intervention phase (T2) with year 9 students in all intervention schools. Approximately 40 students will be selected to participate in the focus groups from all eligible students. Each focus group will comprise approximately four individuals in order to develop themes and generate adequate data. Students will be purposively sampled to ensure a mix of sex, and grouped by level of participation in the GoActive intervention. Subsequent interviews with representatives from all other relevant groups within intervention schools (mentors, teachers and facilitators) will commence in T3. Each focus group (separate for mentors, teachers and facilitators) will comprise 3–8 individuals. An interview guide will be developed and updated as new issues and themes emerge; participants will be encouraged to discuss additional issues. Issues arising will inform the next round of questionnaires and subsequent focus groups, so that additional mechanisms of change can be investigated. In addition to focus groups, individual interviews will be conducted with a purposive sample of inactive and shy Year 9 participants (identified using questionnaire data) at intervention schools to provide a deeper understanding of their intervention experience, and barriers and facilitators to participation (we anticipate these individuals will be more comfortable participating in one-to-one interviews).

At T4, additional semistructured focus groups and interviews with students will explore maintenance of physical activity behaviour change, including who did or did not maintain physical activity behaviour change and why, whether GoActive helped and why or how, and other factors that helped or hindered physical activity maintenance. T2 participants will be reinvited, supplemented by additional students if needed. This gives us a unique opportunity to explore physical activity maintenance across time in the context of a trial and to better understand barriers and facilitators to physical activity maintenance.

### Cost-effectiveness

We will conduct both a within-trial and decision-model-based economic evaluation. The within-trial analysis will be from the cost perspective of the school/local authority. Cost data collected will include intervention-related facilitator time, travel and expenses collected by schools/researchers. Outcomes will comprise change in MVPA and quality-adjusted life-years (QALYs) gained. These will be assessed using the CHU-9D^55^ and converted to health state utilities using UK-specific valuations.^56^ Change in physical activity observed and costs to schools/local authorities will be input into a previously developed model to predict longer-term costs (to the National Health Service (NHS)) and QALYs hence cost-effectiveness from a public sector perspective (defined as local authority and NHS).

Data collection forms and questionnaires for all measurements are available on request from the corresponding author.

### Data management and monitoring

All data will be collected and managed in line with International Conference on Harmonisation Good Clinical Practice guidelines. Real-time entry and retrospective data validation checks will be conducted. All paper-based questionnaire data will be professionally double data entered and a sample verified for accuracy. Data will be stored securely at the MRC Epidemiology Unit, University of Cambridge, UK. The MRC Epidemiology Unit specialist teams will provide support for training, and quality assessment and control of measurements, and this support will ensure that collection, processing, protection and management of data are timely and of high quality. We will ensure that all provided data are treated as confidential and stored securely. Where this is electronic, data are held on secure computer systems with at minimum password access. All identifiable data will be held on a separate computer system with access limited to appropriate staff by group and password permissions. Personal data will be stored and accessed up to 20 years after study completion.

Due to the low-risk nature of the trial, a formal data monitoring committee has not been appointed. However, the Trial Steering Committee (TSC) will receive regular reports from the investigators and will monitor trial progress and conduct. The TSC will consist of an independent chair, one independent expert, two lay representatives (including a representative from educational sector) and at least two investigators; the committee will be at least 75% independent. The study coordinator and a sponsor representative will be invited as observers. The TSC will meet approximately once per year, or more frequently if needed. The TSC is responsible for communicating any issues of concern to the sponsor, specifically where the integrity of the study or data or patient safety could be comprised. The study coordinator will also monitor trial conduct and will report independently to the MRC Epidemiology Unit Clinical Research Manager. Potential harms will be monitored by the study team. These will be reviewed by the study coordinator, principal investigator and TSC, and will include reported adverse events (eg, injuries or psychological indicators such as well-being). While we do not expect harm as a result of the GoActive intervention or this trial, it is insured by the University of Cambridge which would provide compensation in case of harm.

The council-funded intervention facilitators will work closely with mentors and research staff to monitor protocol adherence. Poor adherence will be discussed with the research team and TSC, and strategies will be put in place where necessary. No activities are prohibited during the trial as students are expected to do their normal physical activities, including school PE.

Any protocol amendments will be proposed to the TSC and subsequently altered if necessary before submission to funder National Institute of Health Research(NIHR) for approval. Protocol updates will then be uploaded to the NIHR website and trial registry if relevant.

## Analyses

### Sample size

We aim to detect a 5 min difference in change in MVPA per day at 10-month follow-up, as observed in the pilot study.^26^ A 5 min increase is relevant at population level as it would increase the proportion of adolescents meeting the guidelines of 60 min of MVPA per day from 43% to 50% (based on baseline pilot data), with significant impact on population health.^2^ To estimate the required sample size, the following parameters have been used: power=85%, significance level=5%, SD=17.8 (observed in the GoActive pilot),^26^ intraclass correlation coefficient=0.034 (observed in SPEEDY-3, n=57 schools),^43^ correlation between baseline and follow-up MVPA=0.59 (observed in GoActive pilot, to account for adjustment for baseline MVPA)^26^ and average cluster size=100. Based on these parameters, we estimate n=1310 participants will be required for the primary effectiveness analysis. To account for potential school dropout and an estimated loss-to-follow-up of 30%–40%, we aim to recruit 16 schools with 150 participants (total n=2400; average recruitment per school in pilot=154).^26^ Should a school have >150 students in year 9, we will include all those who assent to measurement.

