### Outcome analyses

The primary efficacy outcome, MVPA, will be compared between intervention and control groups using analysis of covariance, with adjustment for baseline MVPA; robust SEs will be calculated to allow for the non-independence of individuals within each school. Where baseline values of MVPA are missing, the missing indicator method will be used to enable these participants to be included in the analysis.^57^ An estimate of the intervention effect, 95% CI and p value will be calculated. A similar method will be used for the secondary efficacy outcomes. School-level data will also enable analysis of key differences between those participating in the evaluation and the wider school population; for example, patterns of non-response by demographic variables will be explored. Subgroup analyses by prespecified moderators (sex, socioeconomic status, ethnicity, baseline activity level, weight status) will be performed for the primary outcome only. The interaction between randomised group and each moderator will be tested, and if the p value is <0.05, the intervention effect (difference between intervention and control, and 95% CI) will be estimated within each subgroup. The effect on potential mediating variables will initially be assessed as described above. We will subsequently conduct formal mediation analyses using the product of coefficient method^58^ to assess the underlying causal pathways of the intervention.

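### The 1310 pupils said to give 85% power are only about 13 schools of 100; with school-level degrees of freedom they give about 78%, so the room for losing schools is smaller than the figure implies

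*Protocol article*

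**What the plan says.** The Sample size section of the protocol article sets the target: "We aim to detect a 5 min difference in change in MVPA per day at 10-month follow-up". The inputs are "power=85%, significance level=5%, SD=17.8 (observed in the GoActive pilot"), "intraclass correlation coefficient=0.034 (observed in SPEEDY-3, n=57 schools"), a baseline to follow-up correlation of 0.59 to reflect adjustment for baseline, and an average cluster size of 100. From these it states: "Based on these parameters, we estimate n=1310 participants will be required for the primary effectiveness analysis".

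It then explains the recruitment target: "To account for potential school dropout and an estimated loss-to-follow-up of 30%–40%, we aim to recruit 16 schools with 150 participants", which makes 2400 in total. The section does not say how many schools the 1310 corresponds to, or how many schools could be lost.

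Under School randomisation, eight schools go to each condition, stratified by Pupil Premium and county. Under Outcome analyses, the primary comparison is an analysis of covariance, and "robust SEs will be calculated to allow for the non-independence of individuals within each school". No reference distribution is named there.

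**The concern.** Schools are randomised, so the precision of the treatment comparison has to be judged against variation between schools. A design effect inflates the variance correctly, but it leaves the critical value as if hundreds of independent pupils were being compared. With about 13 schools the difference is not trivial: the two-sided 5% critical value is 2.20 on 11 degrees of freedom, against 1.96 for the normal.

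Two statements depend on this. The first is that 1310 pupils, at 100 per school, are enough for 85% power. The second is that recruiting 16 schools covers school dropout as well as pupil loss. If the first is too favourable, the margin behind the second is smaller than it appears, and the trial team could treat the loss of several schools as already covered.

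**Working it through.** **Inputs (all from Sample size).** Difference 5 min; SD 17.8; correlation 0.59; ICC 0.034; 100 pupils per school; 85% power; 5% significance. Sidedness is not stated. Two-sided is assumed, because a one-sided calculation gives 1037 and does not reproduce the stated figure.

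**Step 1: reproduce 1310.**
- Residual SD after baseline adjustment: 17.8 × √(1 − 0.59²) = 17.8 × √0.6519 = 14.37.
- Design effect: 1 + (100 − 1) × 0.034 = 4.366.
- Pupils per arm if independent: 148.4 by the normal formula; 150 by a two-sample t calculation with individual-level degrees of freedom.
- Total: 2 × 148.4 × 4.366 = 1295 (normal), or 2 × 150 × 4.366 = 1310 (t).

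The published figure is therefore the individual-level sample size times the design effect. Other readings do not fit: no baseline adjustment gives 1987, and a change-score variance gives 1630.

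**Step 2: convert to schools.** 1310 / 100 = 13.1 schools.

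**Step 3: power with school-level degrees of freedom.** For k schools of m pupils, SE = 14.37 × √(4 × [1 + (m − 1) × 0.034] / (k × m)). Power comes from a noncentral t with noncentrality 5 / SE and k − 2 degrees of freedom.

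For 1310 pupils at 100 per school, the noncentrality is 3.013. The normal reference gives 85.4%; t on 11 degrees of freedom gives 78.3%. Exactly 13 schools of 100 give 85.1% and 78.0%. Across other choices of degrees of freedom the range is 74.8% (k − 5, charging for the four strata, 13 schools) to 79.0% (k − 1, 1310 pupils).

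**Step 4: the planned design and school loss.** Pupil loss of 40% or 30% from 150 leaves 90 or 105 per school. Power with k − 2 degrees of freedom:

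| Schools retained | 90 per school | 100 per school | 105 per school |
|---|---|---|---|
| 16 | 86.4% | 87.2% | 87.5% |
| 15 | 83.7% | 84.6% | 85.0% |
| 14 | 80.6% | 81.6% | 82.0% |
| 13 | 77.0% | 78.0% | 78.4% |

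With k − 1 degrees of freedom, 15 schools give 84.2%, 85.0% and 85.4% across the three columns. With k − 5, 16 schools give 84.9%, 85.7% and 86.1%.

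**Step 5: schools needed for 85% at 100 per school.** 13 by the normal reference; 15 with k − 1; 16 with k − 2 or k − 5.

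**The case against.** The strongest reply is that nothing was miscalculated. 1310 follows from the stated inputs by a widely used formula, and the design that will actually be run meets its target: 16 schools with 90 to 105 analysed pupils give 86.4% to 87.5%. Even 1310 pupils, if spread over all 16 schools (about 82 each), give 85.6% on 14 degrees of freedom. This stands. It limits the point to the stated requirement at 100 pupils per school and to the dropout allowance; the full design is not at fault. The requirement as written, however, is tied to a cluster size of 100, and at that size it falls about 7 points short.

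A reader might infer that there is no cushion at all and that every one of the 16 schools is needed. The documents do not support this. Fifteen schools give 84.6% at 100 per school and 85.0% at 105 with k − 2 degrees of freedom, or 85.0% and 85.4% with k − 1. One school can be lost at little or no cost relative to the target.

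A reader might also infer that the protocol promises three spare schools. It does not: it makes one combined allowance for school dropout and pupil loss and gives no number of spare schools. Three comes from dividing 1310 by 100 and comparing with 16. The Schools section under Recruitment procedures also provides a waiting list to replace schools that withdraw before randomisation, so only later withdrawals matter, and no rate is given for those.

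Finally, a reader might take the Outcome analyses section to be wrong as well. It names robust standard errors and no reference distribution. That detail is commonly left to a statistical analysis plan, which is not shown, so no error is established there.

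**Conclusion.** The point holds for the stated relation between size and power. At 100 pupils per school, 1310 pupils give about 78% power (75% to 79% across the choices of degrees of freedom), not 85%. A true 5 min effect would be missed about 22% of the time instead of 15%.

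It does not show that the trial is underpowered as planned. With all 16 schools retained, power is about 86% to 88% with k − 2 or k − 1 degrees of freedom. What changes is the tolerance for losing schools after randomisation: almost none of the power target is lost with one school, but two cost about 3 to 4 points and three about 7 to 8.

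The figures assume two-sided testing, equal school sizes, a near-equal split of schools between arms, and the protocol's own SD, correlation and ICC. Unequal school sizes would lower power somewhat further, but the protocol gives no figure from which to say how much.

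**What to change.** Revise the Sample size section as follows:

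- State the requirement in schools as well as pupils, calculated with a t reference on school-level degrees of freedom, and name the degrees of freedom used. At 100 analysed pupils per school, 85% power needs about 15 to 16 schools, depending on that choice.
- Replace the statement that 1310 pupils suffice at a cluster size of 100.
- Report the power of the 16-school design over the expected 90 to 105 analysed pupils per school, and the power if one, two or three schools are lost after randomisation, so that the dropout allowance is explicit.

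This takes a few sentences and no additional schools or pupils. The cost is a less favourable stated figure.

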#### Quantitative analyses

The primary analysis of effectiveness, intermediate and safety outcomes will use an intention-to-treat population, which includes all participants in the group to which they were randomised, regardless of the intervention received. A secondary analysis of efficacy and intermediate outcomes will use a per protocol (PP) population. Inclusion in the PP population will be based on the degree of usage of the intervention website and/or submission of points, and will be defined once clean data are available (but before the start of any trial analyses), when the distributions of degree of website usage can be inspected.

### Outcome analyses

The primary efficacy outcome, MVPA, will be compared between intervention and control groups using analysis of covariance, with adjustment for baseline MVPA; robust SEs will be calculated to allow for the non-independence of individuals within each school. Where baseline values of MVPA are missing, the missing indicator method will be used to enable these participants to be included in the analysis.^57^ An estimate of the intervention effect, 95% CI and p value will be calculated. A similar method will be used for the secondary efficacy outcomes. School-level data will also enable analysis of key differences between those participating in the evaluation and the wider school population; for example, patterns of non-response by demographic variables will be explored. Subgroup analyses by prespecified moderators (sex, socioeconomic status, ethnicity, baseline activity level, weight status) will be performed for the primary outcome only. The interaction between randomised group and each moderator will be tested, and if the p value is <0.05, the intervention effect (difference between intervention and control, and 95% CI) will be estimated within each subgroup. The effect on potential mediating variables will initially be assessed as described above. We will subsequently conduct formal mediation analyses using the product of coefficient method^58^ to assess the underlying causal pathways of the intervention.

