## School randomisation

Schools will be stratified based on Pupil Premium (proxy for socioeconomic status, below/above the county-specific median; for information: https://www.gov.uk/guidance/pupil-premium-information-for-schools-and-alternative-provision-settings) and county (ie, Cambridgeshire or Essex). Randomisation lists for each stratum will be prepared by a statistician, using Stata (ref: StataCorp. 2015. Stata Statistical Software: Release 14. College Station, Texas, USA: StataCorp), after baseline measurements are completed to ensure schools and participants are unaware of their group allocation at baseline. Eight schools will be randomised to deliver the GoActive intervention and eight to a no-treatment control condition. For measurements after randomisation, it will not be possible to blind participants to randomised allocation as the intervention schools will have received the GoActive intervention.

Measurement staff will be blinded to intervention condition throughout the study as they will be trained and work separately from those involved in intervention delivery. Process evaluation with measurement staff will examine the success of blinding.

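### Schools are randomised within county and Pupil Premium strata, but the stated primary model adjusts only for baseline MVPA; adding the two factors, with a small-sample correction, would be a cheap improvement

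*Protocol article*

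**What the plan says.** Under School randomisation the protocol states: "Schools will be stratified based on Pupil Premium (proxy for socioeconomic status, below/above the county-specific median", the second factor being county, with Cambridgeshire and Essex as its levels. A randomisation list is drawn up for each stratum. The allocation is 1:1: "Eight schools will be randomised to deliver the GoActive intervention and eight to a no-treatment control condition".

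Under Outcome analyses, MVPA is to be "compared between intervention and control groups using analysis of covariance, with adjustment for baseline MVPA", and "robust SEs will be calculated to allow for the non-independence of individuals within each school". Secondary efficacy outcomes are to be handled in a similar way. Neither county nor Pupil Premium is named in any outcome model. Socioeconomic status appears there only as a subgroup moderator.

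The Sample size section takes credit for baseline adjustment (correlation 0.59) and none for stratification.

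**The concern.** Stratified allocation makes the arms alike on county and on deprivation as measured by Pupil Premium. If those factors predict follow-up MVPA after baseline MVPA is accounted for, the true variance of the difference between arms falls. A model without the factors leaves their between-school variance in the residuals. A robust standard error clustered on school does not remove it, because it takes no account of the balance within strata. The reported standard error is then larger than the true one, the confidence interval is too wide and power is lost.

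Between-school variance is the larger part of the error here. With 90 students per school, the variance of a school mean is proportional to 0.034 (between schools) plus 0.966/90 = 0.0107 (within schools). What the strata explain of the first term is therefore worth having.

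**Working it through.** **Inputs from the Sample size section.** Difference 5 min; power 85%; significance level 5% (taken as two-sided); SD 17.8; intraclass correlation 0.034; baseline to follow-up correlation 0.59; cluster size 100; 16 schools of 150; loss to follow-up 30–40%.

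**The plan's own figure.**
- Residual variance: 17.8² × (1 − 0.59²) = 206.5.
- Per arm, unclustered: 2 × (1.960 + 1.036)² × 206.5 / 5² = 148.4.
- Design effect: 1 + 99 × 0.034 = 4.366.
- Total: 2 × 148.4 × 4.366 = 1295, or 1301 with rounding per arm, against 1310 stated. The figure reproduces.
- With 16 schools of 100, the SE is √[(2/8) × 206.5 × (0.034 + 0.966/100)] = 1.50. Power is about 87% (t, 14 df) or 91% (normal), without any use of the strata.

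**Assumptions for the comparison.** 90 analysed per school (150 × 0.60); equal school sizes; four strata of four schools, each split 2:2; the intraclass correlation applies to the baseline-adjusted residuals. The share s of between-school residual variance explained by the strata is not in the documents, so it is varied.

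**True SE of the treatment difference** = √{(2/8) × 206.5 × [0.034(1 − s) + 0.966/90]}:
- s = 0: 1.52
- s = 0.10: 1.46
- s = 0.30: 1.34
- s = 0.50: 1.20

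This applies to the unadjusted estimate as well, because the balance comes from the allocation. What differs is the SE that is reported. With the strata left in the residual, the expected residual mean square of the school means at s = 0.30 is 206.5 × (0.0238 + 0.0107) + (16/14) × 0.30 × 7.02 = 9.54. The corresponding SE is √(9.54 × 2/8) = 1.54; the mean SE in simulation is 1.52, against a true 1.34.

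**Simulation on school means.** Unadjusted: a model SE with t on 14 df, and a robust SE with a 16/15 correction and t on 15 df. Adjusted: county and Pupil Premium added, model SE, t on 12 df.

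| Share explained | Type I error, unadjusted t14 | Type I error, robust t15 | Power, unadjusted t14 | Power, robust t15 | Power, adjusted t12 |
|---|---|---|---|---|---|
| 0% | about 5% | 5.5–6% | 87% | 88% | 86% |
| 10% | 4.1% | 4.9% | 87% | 89% | 88% |
| 30% | 2.6% | 3.1% | 88% | 90% | 93% |
| 50% | 1.3% | 1.6% | 90% | 92% | 97% |

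The adjusted t12 test holds about 5% throughout. Break-even against the unadjusted t14 test is near 5% explained. At 0% the critical value moves from 2.145 (14 df) to 2.179 (12 df), which widens the interval by 1.6%.

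**Adding the strata without a correction.** If both factors are added and the same robust SE is kept, type I error is about 8% (t, 15 df) or 10% (normal reference) at every share.

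**The case against.** Four points on the other side deserve weight.

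*The planned test is the robust one, and it is not always conservative.* With a t15 reference it runs slightly above 5% at 0% explained and near 5% at 10%. With a normal reference it runs at roughly 7–8% over that range and 4.5% at 30%. The protocol does not fix the reference distribution. This stands: loss of power and conservatism should not be claimed at small shares. The excess there comes from having 16 clusters, not from leaving out the strata.

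*The size is unknown.* No figure is given for what county and Pupil Premium explain beyond baseline MVPA. Pupil Premium is cut in two at a county-specific median, and baseline MVPA may already absorb part of any effect. This also stands, and is why only a range is given.

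*Adjustment has a price.* It uses two degrees of freedom and, under uncorrected robust SEs, inflates type I error. This stands and shapes the fix.

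*The analysis plan is not shown and may add the factors.* That is possible, but the protocol does more than stay silent: it states the model, its covariate and its variance method. If the analysis plan differs, the protocol wording still needs to be brought into line.

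Three stronger readings are tempting and not supported. A reader might infer that the trial is underpowered; the sample size takes no credit for stratification, and about 87% power remains at 100 per school. A reader might infer biased estimates or extra false positives from the omission; it causes neither. A reader might set 86% (unadjusted, nothing explained) against 93% (adjusted, 30% explained) and read a gain of seven points; stratified allocation already helps the unadjusted analysis, so like for like the gain is 88% to 93%, or 90% to 93% against the robust test.

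**Conclusion.** The point holds as a matter of efficiency and of matching the analysis to the design; it is a cheap improvement and not a flaw that threatens the trial. That the strata are absent from the stated model is plain from the text. The harm is conditional: none below about 5% of between-school residual variance explained, roughly three to five power points at 30%, and five to seven at 50%, with a test that then runs well under its nominal 5%. These figures rest on 90 analysed per school, equal school sizes, a 2:2 split in four strata, and the protocol's own SD, correlation and intraclass correlation.

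**What to change.** In Outcome analyses, name county and Pupil Premium group (two school-level indicators) as fixed effects in the primary and secondary models. In the same sentence, specify a small-sample method for 16 clusters: for example a bias-corrected cluster variance with a t reference on 12 df, or a school-level analysis. The two changes belong together, since the first alone would make the test liberal.

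The cost is wording plus two degrees of freedom, about one power point if the strata explain nothing. Both factors are known for every school at randomisation, so no further data are needed and no values will be missing. Naming them in advance also removes any later choice about covariates.
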